## Abstract

**Background:**

There are limited evidence-based treatment options for adolescents with patellofemoral pain (PFP). Flat, flexible footwear have been shown to reduce patellofemoral joint loading and pain in adults with PFP. The efficacy of this intervention in adolescents with PFP is not established. The primary aim of this study is to determine the feasibility of conducting a large-scale randomised controlled trial (RCT) of the effect of flat, flexible school footwear, when compared to traditional school footwear, in adolescents with PFP. The secondary aim is to describe changes in self-reported outcome measures for adolescents with PFP while wearing flat, flexible footwear when compared to traditional school shoes.

**Methods:**

Twenty-four adolescents with PFP will be recruited from the community. Following baseline assessment, participants will be randomly allocated to receive either (i) flat, flexible school footwear or, (ii) traditional school footwear. Participants will wear the shoe as per school requirements throughout a 12-week intervention period. Feasibility will be assessed with (i) ≥ 75% adherence to allocated shoe wear of their total weekly school wear time, (ii) a recruitment rate of one participant per fortnight, and (iii) a dropout rate of ≤ 20%. Patient reported outcome measures will describe changes in knee pain, function, quality of life and global rating of change at 6 and 12 weeks. Descriptive statistics will be used for the primary outcomes of feasibility.

**Discussion:**

This study will determine the feasibility of conducting a large scale RCT evaluating the effect of flat, flexible school shoes for adolescents with PFP. A full-scale study will guide evidence-based management of adolescent PFP.

**Trial registration:**

Australian New Zealand Clinical Trials Registry reference: ACTRN12621001525875, Date registered: 9^th^ November 2021.

**Supplementary Information:**

The online version contains supplementary material available at 10.1186/s13047-022-00558-z.

## Background

There is a significant increase in the number of musculoskeletal injuries reported at the onset of and during adolescence [1]. A quarter of adolescents aged 12–15 years’ experience knee pain, with patellofemoral pain (PFP) the most prevalent diagnosis [2]. PFP is characterised by pain in and around the patella that is aggravated by weightbearing activities such as running and stair ambulation [3]. PFP in adolescence has substantial implications on long-term physical and mental health [4]. Seventy-percent of adolescents with PFP are likely to cease or reduce their participation in physical activity, compared to 50% of adolescents with other types of knee pain [5]. Adolescents with PFP experience poorer mental health and they are twice as likely to use pain medication regularly when compared to other diagnoses of knee pain [6, 7]. The long-term prognosis of adolescent PFP is poor, with symptoms persisting in up to 91% of adolescent cases after 4–18 years [8, 9].

Despite the burden of adolescent PFP, there is a paucity of studies that have examined treatment options within this cohort. Treatment of adolescent PFP is generally adopted from guidelines implemented in adult studies [10]. As reported in the ‘Best Practice Guide to Conservative Management of PFP’ and an international consensus statement, exercise therapy has been shown to improve pain in the short, medium, and long-term in adults with PFP [10, 11]. However, the efficacy of exercise therapy for adolescents with PFP is not as effective as that reported in adult studies [12]. Matched studies examining exercise therapy in adults and adolescents with PFP reflect this, with 62% of adults reportedly recovering compared with only 38% of adolescents [13, 14]. Several factors may underpin this. Exercise therapy is designed to address strength deficits that are observed in adults with PFP, such as reduced hip abduction and external rotation strength [15, 16]. Adolescents with PFP do not demonstrate hip and knee strength deficits when compared to healthy controls [17, 18]. Therefore, exercise therapy targeted to address strength deficits may be less efficacious in adolescents.

Poor adherence to exercise-based interventions are also reported in adolescents with PFP due to factors such as school commitments, time constraints and boredom with the program [12, 19, 20]. Adolescents with PFP also typically report pain in both knees, with up to 79% reporting bilateral symptoms of PFP compared to 43% of adults with PFP [21]. This bilateral nature may increase the time commitment of prescribed exercise therapy [12, 21]. Given adolescents with PFP do not demonstrate reduced muscular capacity, and their adherence to prescribed exercise therapy may be reduced, alternative treatment options that focus on patellofemoral joint load reduction may be more advantageous within this population.

Flat, flexible footwear have been shown to reduce patellofemoral joint loading during running [22–24], stair descent [25] and jumping [26] in asymptomatic adults as well as adults with PFP [27]. Improvements in PFP symptoms among adults have also been reported when flat, flexible footwear have been used in isolation [27] or when combined with gait retraining [28]. The effectiveness of flat, flexible footwear on patellofemoral joint loads, pain, and function in an adolescent PFP cohort is unknown. Adolescents spend a large proportion of their weekdays attending school in school footwear [29]. School footwear must adhere to school uniform guidelines that most commonly include a low-heeled, leather upper, lace-up or buckle shoe [30]. Activity data shows that adolescents participate in a range of sport and physical activity while at school and 23% meet their daily moderate-vigorous activity targets within school breaks alone [31]. This suggests that a high percentage of total daily physical activity is performed in school footwear during school hours [32, 33]. Wearing a flat, flexible shoe at school may be an alternative management option for adolescents with PFP as shoes address the bilateral nature of adolescent PFP; are likely to have greater adherence than exercise therapy; and are usually worn by adolescents for long periods of time while at school.

Investigating the feasibility of a flat, flexible school shoe for adolescents with PFP is a necessary step toward developing targeted evidence-based management. Early intervention is essential for minimising the potential for chronicity within this population, as well as reducing the significant long-term health-related behaviour changes associated with adolescent PFP [5, 9]. A feasibility trial provides the first step to determining the requirements and potential application of a future large scale randomised controlled trial (RCT) [34]. The primary objective of this study is to determine the feasibility of conducting a large scale RCT on the effect of a flat, flexible school shoe in adolescents with PFP. The secondary outcome is to describe changes in knee function and pain with the use of a flat, flexible school shoe compared to a traditional school shoe in adolescents with PFP.

## Methods

### Experimental/trial design

This study is an assessor blind, randomised, feasibility trial, with two parallel groups of adolescents with PFP. The research proposal has been developed in consultation with the Standard Protocol Items: Recommendations for Interventional Trials (SPIRIT) 2013 statement [35] and the Consolidated Standard of Reporting Trials (CONSORT) 2010 guidelines for randomised pilot and feasibility trials [36].

Ethical approval was granted through the Deakin University Human Research Ethics Committee (2021–135). The trial was prospectively registered on the Australian and New Zealand Clinical Trials Registry (ACTRN12621001525875, Date registered: 9^th^ November 2021). Written informed consent will be obtained from all participants and their parents/guardians prior to participation within the study.

### Participants

Male and female adolescents will be eligible for inclusion if they meet the following criteria: (i) aged between 12–18 years, (ii) have PFP from a non-traumatic onset of at least six weeks duration, (iii) have pain ≥ 30/100 mm (mm) on a visual analogue scale (VAS), and (iv) have knee pain which is aggravated by activities that load the patellofemoral joint (e.g., squatting, stair ascent or descent, running).

Adolescents will be excluded if they (i) have pain at sites other than the anterior knee (e.g., other knee structures, hip, pelvis, lumbar spine), (ii) have a history of hip, knee or spine surgery, or other suspected knee joint pathology (e.g., Sinding Larsen Syndrome, Osgood Schlatter’s Disease), (iii) have planned lower limb surgery, (iv) have a neurological condition or systemic arthritis, (v) are currently wearing flat flexible footwear for school and/or (vi) have any condition which prevents them from wearing flat flexible footwear (e.g., calcaneal apophysitis).

Adolescent volunteers will be recruited from the community using a targeted comprehensive recruitment strategy with proven efficacy in previous studies of PFP [28, 37, 38]. Recruitment strategies will include paid social media advertising, dissemination through social media networks and flyers displayed at local sports medicine and allied healthcare clinics, footwear stores and sporting clubs/recreational facilities where PFP is likely to be prevalent. Eligibility criteria are based on previous high quality RCTs for PFP [13, 37].

To observe feasibility outcome of adherence, we plan to recruit 24 participants with PFP. A minimum of 23 participants are required to observe the feasibility outcome of adherence ≥ 75% allocated shoe wear indicating progression to a full trial is feasible. If adherence to allocated shoe wear is ≤ 50% (i.e., two school days per week, excluding a sporting day) progression to a main trial is not feasible (alpha < 0.05, β 0.2) [37, 39, 40].

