### Outcomes measures

#### Primary outcome measures

The primary outcome from this study is to determine the feasibility of conducting a full-scale RCT in adolescents with PFP. Feasibility will be assessed by the following outcome parameters; (i) adherence to allocated shoe wear of ≥ 75% of their total weekly school shoe wear time, (ii) a recruitment rate of one participant per fortnight, and (iii) a dropout rate of ≤ 20%. Success of blinding and participants’ expectations of treatment will be evaluated using the Credibility and Expectancy Questionnaire [48]. This will be completed at the end of the baseline assessment immediately after participants have been fitted into their shoes and then at the end of week one [37].

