### Adverse events

For the study duration participants will be advised to report information on adverse events and/or use of concomitant care within their weekly log sheet. Participants will be encouraged to report any discomfort they experience to the research team. If required, participants will attend an additional appointment with the research team to discuss any discomfort they may be experiencing. In this instance, standard clinical practice principles will be applied. The researcher may recommend strategies to improve the adaptation (e.g. a return to their regular footwear until pain settles). These events will be recorded as adverse events and if the discomfort cannot be reduced or tolerated, the participant will be encouraged to return to using their normal footwear and the individual’s participation with the intervention will be ceased.

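### Recruiting 24 against a stated minimum of 23 leaves room for one loss, while the trial accepts up to four dropouts, so the stated beta of 0.2 does not hold at the dropout it tolerates

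*Protocol article*

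**What the plan says.** The Participants section of the protocol article sizes the trial on adherence alone: "To observe feasibility outcome of adherence, we plan to recruit 24 participants with PFP". It continues: "A minimum of 23 participants are required to observe the feasibility outcome of adherence" at or above "75% allocated shoe wear indicating progression to a full trial is feasible". The opposite boundary is adherence at or below "50% (i.e., two school days per week, excluding a sporting day) progression to a main trial is not feasible". The error rates are given as "alpha < 0.05, β 0.2"; sidedness is not stated. No dropout allowance is given to link 23 to 24.

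The Primary outcome measures section lists the other two feasibility criteria as "a recruitment rate of one participant per fortnight, and (iii) a dropout rate of" at most 20%. The Abstract repeats them.

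Three further places bear on what a lost participant contributes:

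- Outcome assessment: adherence data come from a weekly log of the shoe worn each day and the hours worn, kept throughout the study.
- Adverse events: if discomfort cannot be reduced or tolerated, the individual's "participation with the intervention will be ceased".
- Planned statistical analysis: feasibility outcomes are reported descriptively against the criteria.

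**The concern.** Three figures fixed by the same document do not fit together: a minimum of 23, a recruitment target of 24, and a tolerated dropout of 20%. If 23 is a real design minimum, a second loss breaches it, yet the trial would still count a third and a fourth loss as success on the dropout criterion.

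Adherence is the first-listed feasibility criterion and the only one used to size the trial. The Participants section ties it directly to whether a main trial should follow. If the number contributing to it falls to 20, the decision rests on less information than the stated error rates imply, and a reader of the results would not know this.

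**Working it through.** **Inputs.** Recruitment 24, minimum 23, adherence 0.75 (feasible) against 0.50 (not feasible), alpha 0.05 and beta 0.2 (all Participants section); dropout ceiling 20% (Primary outcome measures). Assumptions: one-sided alpha, one yes/no adherence result per participant, both arms pooled.

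**Step 1: reproduce 23.** For an exact one-sample binomial design, take the smallest cut r with P(X ≥ r | n, 0.50) ≤ 0.05, then power = P(X ≥ r | n, 0.75). The smallest n with power of at least 0.80 is 23: r = 16, alpha 0.0466, power 0.8037. The normal approximation agrees: [(1.645 × 0.5 + 0.842 × 0.433) / 0.25]² = 22.5, rounded up to 23. Two-sided versions give 29 (normal) or 30 (exact). So the stated 23 is reproduced, and one-sided alpha is the reading that reproduces it.

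**Step 2: margin against tolerance.**

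- Margin: 24 − 23 = 1, and 1/24 = 4.2%.
- Tolerated losses: 4/24 = 16.7% passes and 5/24 = 20.8% fails, so up to four losses, leaving 20.
- Inflating 23 for 20% dropout: 23/0.8 = 28.75, so 29.

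**Step 3: power when those lost give no adherence value.**

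| Evaluable | Losses from 24 | Cut | Exact alpha | Power |
|---|---|---|---|---|
| 24 | 0 | 17 | 0.032 | 0.766 |
| 23 | 1 | 16 | 0.047 | 0.804 |
| 22 | 2 | 16 | 0.026 | 0.699 |
| 21 | 3 | 15 | 0.039 | 0.744 |
| 20 | 4 | 15 | 0.021 | 0.617 |
| 19 | 5 | 14 | 0.032 | 0.668 |

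The pattern is uneven because the cut moves in whole participants. Nineteen is just past the dropout ceiling and is shown because 24 × 0.8 = 19.2. Averaged over random dropout at 20%, power is about 0.67.

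**Step 4: chance of keeping at least 23 of 24.** With dropout risk d, this is (1 − d)^24 + 24 d (1 − d)^23.

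- d = 0.20: 0.0047 + 0.0283 = 0.033
- d = 0.10: 0.0798 + 0.2127 = 0.292
- d = 0.05: 0.2920 + 0.3688 = 0.661

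**Step 5: effect of the denominator.** Suppose 12 of 24 are truly adherent (50%) and four non-adherent participants are lost. If the four are excluded, observed adherence is 12/20 = 60%. Treating 60% as the adherence rate among the 20, the chance of reaching 15/20 is 12.6%, against 2.1% at a rate of 50%. If instead the four are counted as non-adherent, the denominator stays at 24 and this inflation does not arise. The criterion then becomes hard to meet: with 75% adherence in the remaining 20, the chance of at least 17 adherent is 22.5%.

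**The case against.** The 20% is a ceiling for progression, not a forecast. With no dropout or one, both the dropout criterion and the minimum of 23 are met, so a reader who inferred that the two cannot both be satisfied would be wrong. The Participants section also asks for 23 participants, not 23 completers; if everyone randomised contributes, 24 exceeds 23 and the shortfall disappears. This stands, and it makes the loss of power conditional.

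A reader might also infer that the adherence figure will be biased upward because those who cannot tolerate the shoe drop out of it. The document does not support that. The Adverse events section ends participation in the intervention, not in the study. The weekly log records which shoe was worn, so a participant back in other footwear who keeps logging lowers the adherence figure. Those who leave altogether still have logs from before they left. Nothing limits adherence to completers, and the handling rule may sit in an analysis plan that is not shown. Nor may a result between the two boundaries, such as 15/24 = 62.5%, be called a failure: the article assigns it no decision.

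The fall from 0.80 to 0.62 partly reflects discreteness. At 20, a cut of 14 would give power 0.786 at alpha 0.058, and power at 24 with no loss is already only 0.77. The planned analysis is descriptive, so power here describes the design justification and not a test that will be run. All of this is fair. None of it explains how 23, 24 and a 20% tolerance were meant to fit together.

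**Conclusion.** The point holds in a limited form. The stated minimum of 23 is a genuine power-based figure. The target of 24 covers one loss, and the trial's own dropout criterion covers four. It can pass that criterion and miss its minimum. At two to four losses the power behind the adherence criterion is 0.62 to 0.74 and not the 0.80 implied by beta 0.2; even at 24 with no loss it is 0.77 with a cut that respects alpha 0.05. At a true 20% dropout rate the chance of keeping 23 is 3%, and at 10% it is 29%.

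The power figures rest on one-sided alpha, a binary outcome per participant pooled over arms, and no usable adherence value from those lost. Upward bias remains only a possibility that depends on an exclusion rule the article does not state. The point is worth correcting because adherence drives the progression decision and the correction is cheap; it does not undermine the design.

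**What to change.** 1. Keep 24. In the Participants section, replace the minimum of 23 at beta 0.2 with the operating characteristics at 24 (cut 17, alpha 0.032, power 0.77) and across 19 to 23 evaluable, and state that alpha is one-sided.
2. Compute adherence over all randomised participants. Use the logs completed before dropout, and count school weeks known to follow cessation of the intervention as not wearing the allocated shoe.
3. Report two sensitivity analyses: log-completers only, and missing logs counted as non-wear. The second should not be the main analysis, because it equates not reporting with not wearing and makes dropout count against two criteria (the 22.5% in the working).

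The cost is wording in the sample-size and primary-outcome sections, with no extra recruitment. The price is a lower stated power and, probably, a somewhat less favourable adherence figure. Recruiting 29 would be the alternative if the sponsor wants to keep 23 evaluable at 20% dropout; it is not needed if the denominator is all randomised.

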### Planned statistical analysis

Data processing, data entry and data analysis will be performed by an assessor who is blinded to group allocation. All statistical analysis will be performed using SPSS version 27.0 or later (SPSS, Chicago, USA). Descriptive statistics will be used for the primary outcomes of feasibility and reported in relation to the pre-specified feasibility criteria. Patient reported outcome measures will be described with means and standard deviations for continuous data and counts and percentage for categorical data.

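### The stated β of 0.2 does not describe the written adherence rule: the sample size fits a cut-off near 70%, while the rule asks for an observed 75% or more

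*Protocol article*

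**What the plan says.** The sample-size paragraph (Protocol article, Methods, Participants) states "we plan to recruit 24 participants with PFP" and then "A minimum of 23 participants are required to observe the feasibility outcome of adherence". Its go condition is "adherence ≥ 75% allocated shoe wear indicating progression to a full trial is feasible". Its no-go condition begins "If adherence to allocated shoe wear is ≤ 50" (per cent), which it glosses as two school days per week with a sporting day left out. The error rates attached to this pair are "alpha < 0.05, β 0.2". No test or cut-off count is named, and no outcome is given for results between 50% and 75%.

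Primary outcome measures defines the criterion as "adherence to allocated shoe wear of ≥ 75% of their total weekly school shoe wear time". Planned statistical analysis adds: "Descriptive statistics will be used for the primary outcomes of feasibility and reported in relation to the pre-specified feasibility criteria". So the only go rule in the text is that observed adherence reaches 75%.

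**The concern.** A sample size with an alpha and a β belongs to a particular decision rule. In a one-sample test of 50% against 75%, the success cut-off lies between the two values, and the 80% power is the chance of passing that cut-off when the truth is 75%. If the bar is moved up to 75%, the observed value has to reach its own true value, which happens only about half the time. The printed β would then not be the β of the rule to be applied.

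Feasibility is the primary objective, and adherence is the only one of the three feasibility criteria that carries error rates. A reader would take the paragraph to mean that true adherence of 75% leads to a go about 80% of the time. If that is not so, the team may reach the end of the study with a result such as 17 of 24, which passes the test behind the sample size but fails the written rule, and have to choose between the two after seeing the data.

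**Working it through.** **Inputs.** From Participants: planned n = 24, minimum n = 23, no-go value p0 = 0.50, go value p1 = 0.75, alpha 0.05, β 0.2. From Planned statistical analysis: descriptive comparison with the criteria. Assumption for steps 1 to 4: adherence is a binomial proportion, X adherent out of n.

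**1. Reproducing 23.** Normal approximation, one-sided:

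n = [(z₀.₉₅·√(p0(1−p0)) + z₀.₈₀·√(p1(1−p1))) / (p1 − p0)]² = [(1.645 × 0.500 + 0.842 × 0.433) / 0.25]² = 22.5, so 23.

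The arcsine version gives 22.6, also 23. For the exact binomial test, take for each n the smallest r with P(X ≥ r | 0.50) ≤ 0.05, then find the smallest n with P(X ≥ r | 0.75) ≥ 0.80. The result is n = 23, r = 16 (69.6%):

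- P(X ≥ 16 | 23, 0.50) = 0.0466
- P(X ≥ 16 | 23, 0.75) = 0.8037

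The two-sided normal version gives 28.9, so 29. The plan's figure is therefore a one-sided one.

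**2. The written rule, observed 75% or more.** The required count is the smallest r with r/n ≥ 0.75. For n = 23, 17/23 is 73.9% and falls short, so r = 18. For n = 24, 18/24 is exactly 75%, so r = 18.

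| True share | P(go), n = 23 (≥18) | P(go), n = 24 (≥18) |
|---|---|---|
| 0.50 | 0.005 | 0.011 |
| 0.75 | 0.468 | 0.607 |
| 0.80 | 0.69 | 0.81 |
| 0.85 | 0.88 | 0.94 |
| 0.90 | 0.98 | 0.99 |

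At the alternative that reproduces 23, the chance of missing a go is 1 − 0.468 = 0.53 or 1 − 0.607 = 0.39, not 0.2. An 80% chance of a go needs a true share of about 0.826 (n = 23) or 0.797 (n = 24). If dropout at the tolerated 20% left 20 or 19 evaluable, P(go) at a true 75% would be 0.617 (≥15/20) or 0.465 (≥15/19).

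**3. Where the misses fall, at a true 75%.**

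- n = 24: P(X ≤ 12) = 0.007; P(13 ≤ X ≤ 17) = 0.385
- n = 23: P(X ≤ 11) = 0.005; P(12 ≤ X ≤ 17) = 0.527

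Almost every miss is a result with no assigned outcome.

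**4. The test cut-off at the planned 24.** The one-sided 5% cut-off is 17/24 (70.8%), with alpha 0.032 and exact power 0.766.

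**5. The other unit.** If adherence means the mean percentage of weekly wear time, a sample size needs an SD. The article gives none, so 23 cannot be checked on that reading. For a roughly symmetric sample mean (assumed), P(mean ≥ 75% | true mean 75%) is about 0.50 whatever the SD.

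**The case against.** The best reply is that the unit is inferred. Primary outcome measures defines 75% as a share of weekly wear time, and Participants explains 50% in school days. No section says what share of participants must be adherent. That stands: every count above depends on the participant reading. However, 23 reproduces only when the percentages are treated as proportions, and the mismatch remains on the wear-time reading (step 5).

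A second reply is that the shortfall is easily overstated. This also stands in part. A reader might infer that a trial with adequate adherence gets a go only about half the time. The article does not support that: 47% belongs to n = 23, the planned 24 gives 61%, and both hold only at the 75% boundary. At n = 24 and a true 85% to 90%, the rule gives a go 94% to 99% of the time. A reader might also infer that the rule rejects good shoes. It does not: a formal no-go at a true 75% has probability under 1%, and the criterion governs progression to a full trial. The written rule is also strict against poor adherence, with a 1.1% chance of a go at a true 50%.

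Third, it is tempting to call 77% power at n = 24 a further error. It is not one. The article attaches its error rates to the minimum of 23, where exact power is 0.80, and the drop at 24 comes from the discreteness of the exact test. The unstated sidedness and the absence of a confidence interval are details a condensed article may leave to the full protocol, and are not part of this point.

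Finally, a descriptive report is normal for a feasibility study. That does not answer the point, which is that the sample size, error rates and decision rule printed together do not fit.

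**Conclusion.** The point holds in a limited form. The minimum of 23 is correct for a one-sided test of 50% against 75%, but β 0.2 is not a property of the rule as written. At a true 75% the chance of a go is 47% (n = 23) or 61% (n = 24) rather than 80%, and at a true 80% it is 69% or 81%. At n = 24 and a true 75%, 39% of trials would end between the two thresholds, where the article gives no decision. These figures assume a share of participants with independent binomial outcomes and, for 61%, all 24 evaluable. On a mean wear-time reading, the chance at the boundary is about 50%. This is a wrongly stated property of the adherence rule. It is not an error in the sample size, and it has no bearing on safety or on the secondary outcomes.

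**What to change.** State the unit of adherence. If a share of participants is meant, also define what makes a participant adherent. Then make the rule and the error rates agree, in one of two ways:

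- **Adopt the cut-off behind the sample size.** Go at 16 or more of 23 (one-sided alpha 0.047, power 0.80), or at 17 or more of 24 (one-sided alpha 0.032, exact power 0.77).
- **Keep observed 75% or more.** Replace β 0.2 with the rule's actual properties at n = 24 (61% chance of a go at a true 75%, 1.1% at a true 50%), and assign an outcome to results between 50% and 75%.

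If adherence is a mean wear-time percentage, these counts do not apply. In that case give the assumed SD and the test from which 23 follows, and the properties of the rule on that scale.

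The cost is rewording the sample-size paragraph and the progression rule, with no extra participants. The downside is a less favourable stated figure, except for the 16 of 23 cut-off, which keeps 0.80. The choice should be recorded before adherence data are seen.
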